##### Feasibility of VIG Remote Implementation—Intervention Fidelity

Fidelity will be measured using the VIG-Skills Development Scale (SDS) [64]. This tool provides a structured assessment of VIG skills and is typically used in training and reflective practice to ensure practitioners’ fidelity to the therapeutic model, which emphasizes a strengths-based and balanced approach. The VIG-SDS will be used to measure the fidelity of VIG implementation by reviewing practitioners’ selection of video clip moments during the shared review, which is the meeting between the VIG practitioner and the parent (see the “Intervention” section). A total of 25 VIG cycles will be selected from the 75-125 cycles likely generated during the study. Fidelity will be assessed based on the percentage of reviewed cycles achieving a VIG-SDS score that corresponds to the expected level for the practitioner’s training.

##### Feasibility of Remote Implementation—Intervention and Study Processes

Guided by the Medical Research Council framework for process evaluation [65], the analysis will integrate both bottom-up and top-down approaches to identify key themes emerging from the data across the process evaluation domains of context, implementation, and mechanisms of impact. Satisfaction with specialist mental health service input will be measured by summing the 9 items from the Experience of Service Questionnaire (ESQ) and comparing the results between the 2 groups [61].

##### Health Economics Data Analysis

The health economic analysis will adopt a health and social care perspective. Costs associated with VIG practitioners and other health and social care service usage will be calculated using unit costs from health and social care sources [66]. Health and social service utilization, as well as medication use, will be captured using the CA-SUS [60]. The total cost of remote VIG delivery will be estimated based on the amount of time VIG practitioners spend on delivery and the number of completed VIG sessions or cycles.

### Participant Compensation

A small monetary compensation, in the form of a gift voucher, will be provided to participants after each instance of data collection (screening, baseline, 3-month follow-up, 6-month follow-up, and qualitative interview).

### Patient and Public Involvement

During the development of the study protocol, interviews were conducted with parents and VIG practitioners who had experience with remote VIG. Two parents who had received VIG remotely through their Educational Psychology service were interviewed, and 1 family had experience with an LD CAMHS referral while also receiving remote VIG from Educational Psychology. Parents shared their experiences and reflected on the process and perceived impacts, which contributed to the draft logic model and helped researchers identify additional outcomes for measurement, such as parenting efficacy. Parents questioned whether the effects of VIG were sustained in the medium term and expressed a desire for support that focused more on the child. This raised concerns about the acceptability of a parent-focused therapy such as VIG within a specialist CAMHS setting. Consequently, acceptability was considered the primary outcome of the feasibility study.

Consultations were also conducted with several VIG practitioners experienced in delivering VIG remotely, some of whom had worked with families of children with IDs. They emphasized that VIG is highly feasible for these families, even in a remote setting, and expressed support for its adoption by more services to improve accessibility.

During the conduct of the study, a Parent Carer Advisory Group (PCAG) consisting of 10 parents of children with IDs will be established to provide guidance on study materials and develop a participant recruitment video explaining the study. The PCAG will advise on recruitment materials, processes, data analysis, and dissemination of content and strategy. Additionally, 2 parents from the group will contribute directly to the academic paper during the dissemination phase. The study’s approach to patient and public involvement is informed by Staniszewska et al [67].

### Data Management and Storage

Investigators and research staff will adhere to the Data Protection Act 2018 and General Data Protection Regulation (GDPR) guidelines for handling personal information throughout the study. Qualtrics, a secure and GDPR-compliant platform, will be utilized for online data collection. Personal information will be kept separate from other data, with participant IDs linked to pseudonyms stored in a separate location. Transcripts and verbatim quotes will be pseudonymized, and audio recordings will be deleted after transcription. All data will be stored securely with password protection on study host servers. Access to participant-identifying information will be restricted to designated research staff. Pseudonymized data will be transferred securely between NHS and collaborating organizations for analysis. Personal identifying information will be retained until the study’s completion, while pseudonymized data will be stored for at least 20 years. Participants will be informed of these procedures in the PIS.

### Safety Reporting

In the event that any adverse events or serious adverse events related to the intervention or research procedures occur, the chief investigator and study coordinator will be informed through the completion of an adverse event/serious adverse event form. All events will be reported immediately, and within 24 hours of becoming aware of the event, to the sponsor by the study team. All events will be assessed at each follow-up time point, and intervention delivery staff will be trained to report these directly to the study team at any time during the study.

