**Conclusions:**

The study is the first randomized evaluation of VIG as offered to parents of children with ID who have been referred to specialist mental health settings. The outcomes from this feasibility trial will inform the decision to proceed with a definitive trial, using a traffic light system to evaluate recruitment, retention, and VIG completion rates alongside qualitative insights and economic evaluations.

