## Introduction

### Background

Around 300,000 children in England have an intellectual disability (ID) [1]. ID often co-occurs with other neurodevelopmental conditions, such as autism. Children with IDs are 3-4 times more likely to exhibit challenging behaviors and mental health problems compared with typically developing children. By the age of 5 years, up to 88% of these children show clinical levels of hyperactivity, conduct problems, and emotional issues [2-5]. By mid-childhood (ages 11-12 years), challenging behaviors and mental health problems remain significantly higher in children with IDs compared with typically developing children [4,6].

The term “behaviors that challenge” is specifically used in relation to individuals with IDs or other groups who may have difficulty communicating. It refers to behaviors that, due to their frequency or intensity, place the individual or those around them at risk of harm or exclusion [7,8]. The term emphasizes that these behaviors pose a challenge to services, rather than being inherent problems within individuals with IDs. The term encompasses a diverse range of phenotypically different behaviors (eg, self-injury, aggression), defined by their impact on the environment. In ID, there is evidence of a close association between these behaviors and mental health problems [9].

Parenting and the quality of the parent-child relationship are risk factors for challenging behaviors and mental health problems in these families [10-13]. Children with IDs are at higher risk of experiencing negative parenting and poorer parent-child relationships [12]. The COVID-19 pandemic has further exacerbated these difficulties, leading to an increase in child mental health problems and challenging behaviors, a decline in parental mental health, and additional strain on family relationships due to service disruptions and restrictions [14].

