Health economics data will be collected through telephone-based interviews with participants, conducted at baseline and at the 6-month follow-up, as well as through an online survey completed by clinical staff at the 3-month follow-up. Health and social care utilization will be captured via the telephone interview by adapting the Child and Adolescent Service Use Schedule (CA-SUS) for this study. This questionnaire has been previously adapted for this population [14] and includes items related to primary and secondary care services, as well as medications used over the past 6 months. Service use will be costed using unit costs from the Personal Social Services Research Unit, while medication costs will be determined using the British National Formulary. The CA-SUS will aim to collect all relevant health and social care utilization data, including any service use components that may overlap between VIG and TAU interventions. Costs associated with the delivery of VIG will be gathered through an online survey completed by staff. This survey will collect data on staff salary banding and the number of hours spent on delivery-related tasks.

The economic evaluation will be conducted from a health and social care perspective; therefore, recruitment costs will be excluded.

The secondary outcomes will be analyzed as described in the following sections.

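### Event forms are tied to relatedness and any-time reporting runs only through VIG staff, so adverse event counts will not be comparable between arms

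*Protocol article*

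**What the plan says.** The Safety Reporting section of the protocol article makes four statements that bear on this point.

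- **Trigger for a form:** if "any adverse events or serious adverse events related to the intervention or research procedures occur, the chief investigator and study coordinator will be informed" through an adverse event or serious adverse event form.
- **Sponsor report:** "All events will be reported immediately, and within 24 hours of becoming aware of the event, to the sponsor by the study team".
- **Scheduled assessment:** "All events will be assessed at each follow-up time point". This is not limited to one arm.
- **Any-time route:** "intervention delivery staff will be trained to report these directly to the study team at any time during the study". No matching route is named for TAU families.

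The section does not say who judges relatedness, or whether that judgement comes before or after the form is completed.

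Other parts of the article give the context. The Randomization section sets the arms as VIG plus TAU against TAU, with 50 parents allocated 1:1 (Study Design). The Background section describes behaviors, self-injury and aggression among them, that "place the individual or those around them at risk of harm or exclusion". The CA-SUS, given at baseline and 6 months (Table 2), "includes items related to primary and secondary care services, as well as medications used over the past 6 months". The Expected Findings section presents the trial as a step towards the parameters that a definitive trial needs.

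**The concern.** Relatedness is the only stated condition for completing a form. A TAU family cannot have an event related to an intervention it did not receive. If the condition governs the whole section, TAU events count only when they are tied to questionnaires, interviews or other research tasks, while VIG-arm events can also count through the intervention. The any-time route through delivery staff adds a second difference, because it exists only where VIG is delivered.

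This matters more than usual in this population. Crises, self-injury and aggression are part of the background, so the cause of a single event is hard to judge case by case. A concurrent control arm observed in the same way is what separates background from effect.

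Two things are at stake. Any table of adverse events by arm would reflect the recording rule as well as what happened to families. The rate of serious events under TAU, useful for planning safety monitoring in the definitive trial, would not be estimated.

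**Working it through.** The plan gives no event rate and no safety figure, so there is nothing of its own to reproduce. The check compares two readings of the section, then uses assumed rates to show what follows.

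**1. Two readings of the Safety Reporting section**

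| | Later sentences refer back to related events | Later sentences mean every adverse event |
|---|---|---|
| VIG arm: recorded | events related to VIG or to research procedures | every event |
| TAU arm: recorded | events related to research procedures only | every event |
| Fit with the opening trigger | consistent | contradicts it, because the relatedness condition then does nothing |
| Any-time route | VIG delivery staff only | VIG delivery staff only |

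The left column is the more natural reading. The final clause also refers back, since it tells staff to report events already mentioned. Under either reading the any-time route is one-sided, so ascertainment between visits differs by arm.

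**2. What the filter does to counts (assumed rates)**

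Inputs: n = 25 per arm (50 parents, 1:1). Assumed: p, the proportion of families with a serious event over 6 months; r, the share of VIG-arm events called related. Research-procedure events are set to zero in both arms for simplicity.

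Recorded in VIG = n × p × r. Recorded in TAU = 0.

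| True rate, VIG vs TAU | True events | r = 10% | r = 20% | r = 50% |
|---|---|---|---|---|
| 20% vs 20% (no effect) | 5 vs 5 | 0.5 vs 0 | 1 vs 0 | 2.5 vs 0 |
| 40% vs 20% (doubling) | 10 vs 5 | 1 vs 0 | 2 vs 0 | 5 vs 0 |

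For example, 25 × 0.20 × 0.20 = 1 and 25 × 0.40 × 0.10 = 1. The same record, 1 versus 0, arises with no effect and with a doubling. The filter can hide an excess or create the appearance of one. Halving the assumed rates halves every entry and leaves that conclusion unchanged.

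**3. What complete recording would and would not give**

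Power for a two-sided 5% comparison at 25 per arm, normal approximation: Φ[(|d| − 1.96 × SE₀) / SE₁], where d is the difference in rates, SE₀ uses the pooled rate and SE₁ the separate rates.

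- 10% vs 20%: SE₀ = √(2 × 0.15 × 0.85 / 25) = 0.101; SE₁ = √((0.09 + 0.16) / 25) = 0.100; power = Φ(−0.98) = 16%.
- 5% vs 10%: SE₀ = 0.0745; SE₁ = 0.0742; power = Φ(−1.29) = 10%.

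For 80% power these comparisons need 199 and 435 per arm. Zero events in 25 still leaves a one-sided 95% upper bound of 1 − 0.05^(1/25) = 11.3%. Complete recording therefore gives descriptive background rates only.

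**4. What the CA-SUS can supply**

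It is administered at baseline and 6 months without restriction by arm, and no relatedness judgement stands in front of it. Its limit is retention. At the green threshold of 70%, 0.70 × 50 = 35 families, about 17 or 18 per arm; at 60%, the boundary between amber and red, 30 families.

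**The case against.** The strongest reply is that the section says more than its first sentence. The scheduled assessment covers all events and is not limited by arm, and the sponsor report also refers to all events. On that view both arms are covered. This stands as a possible reading, but it conflicts with the trigger in the same section, so the text still has to be reconciled. It also leaves the one-sided any-time route untouched.

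A reader might also infer stronger conclusions, which the document does not support:

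- **That TAU events are excluded by definition.** They are not. Events tied to research procedures are reportable in both arms.
- **That VIG practitioners decide causality.** The section names them as a reporting route, not as assessors. It names no assessor.
- **That harm in the VIG arm would be invisible.** Table 2 lists the DBC-2 (baseline and 6 months) and the PHQ-4 (baseline, 3 and 6 months) without restriction by arm. These can show worsening child behavior or parental mental health. They do not count discrete events such as admissions.
- **That the CA-SUS serves costing only.** The overview of secondary outcomes also gives it the purpose of testing whether service use can be measured in both groups.
- **That this wording is why the trial cannot show whether VIG harms families.** The trial has no comparative safety objective (Objective section) and no between-arm power calculation (Sample Size and Power). At 25 per arm it could not settle that question under any recording rule.

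Lastly, this is a condensed article. Event definitions and the causality assessor may be in the full protocol, and their absence here is not counted. The trigger and the any-time route, however, are stated in this article.

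**Conclusion.** The point holds in a limited form. On the natural reading, the stated rule records TAU events only when they are tied to research procedures, so event counts are not comparable between arms and the TAU background rate of serious events is not estimated. On the other reading the section contradicts its own trigger. The one-sided any-time route remains on both.

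The size cannot be fixed from the document. The illustration, in which 1 versus 0 is compatible with both no effect and a doubling, rests on assumed event rates of 20% and 40% and assumed relatedness shares of 10% to 50%. It shows how the filter works and is not an estimate. The primary feasibility outcomes are unaffected. What is affected is any presentation of adverse events by arm and the safety planning for the definitive trial.

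**What to change.** 1. **Safety Reporting:** state that serious adverse events are recorded in both arms, by the same method, at each follow-up, regardless of relatedness, and that relatedness is assigned after recording. Make clear which events the later sentences cover. Leave the 24-hour report to the sponsor as it stands.
2. **CA-SUS:** from the 6-month interview, tabulate by arm the number of families reporting relevant secondary-care contacts, with the number who completed the interview as denominator. Label it a descriptive harm indicator that does not depend on a relatedness judgement. Show it next to the progression criteria.
3. **Where collection is already past:** the Results section says recruitment is complete, and six months from March 2024 is about September 2024. Report which recording rule was applied in practice, and do not present adverse event counts as a between-arm comparison. Carry item 1 into the definitive trial.

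The cost is a wording change, a few extra forms for events that prove unrelated, and one table from data the trial already collects. Items 2 and 3 are the most practical steps now.

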## Results

The study recruitment period was planned from December 2022 to March 2024. Recruitment has now been completed and analyses are planned to be completed by November 2024. The first results are expected to be available in 2025.

## Discussion

### Expected Findings

The findings from this feasibility trial are expected to provide valuable information about the acceptability and feasibility of VIG for parents of children with IDs within specialist mental health services. As the first randomized evaluation of VIG in these settings and for this population, no hypotheses can be made regarding the level of acceptability of the intervention or the feasibility of its remote delivery and evaluation. Previous research has emphasized the value of video feedback interventions, such as VIG, in improving parent-child interactions, which are crucial for supporting the mental health and behavioral development of children with IDs [29,30]. However, a previous single-group feasibility study of VIG with a different population (parents of infants) faced difficulties with recruitment and retention, despite high levels of acceptability for VIG (which was delivered face-to-face) [44]. Therefore, conducting a feasibility RCT is a necessary step in determining feasibility, acceptability, and other parameters required before a definitive trial.

### Conclusions

This study represents the first randomized evaluation of VIG offered remotely to parents of children with IDs referred to specialist mental health settings. The findings regarding acceptability and feasibility will inform the design of a definitive randomized trial, should the progression criteria be met.

### Dissemination Plan

The results of this feasibility trial will be disseminated as noted in Textbox 3.

Dissemination of the trial results.
**1. Parent Carer Advisory Group Involvement**
The Parent Carer Advisory Group (PCAG) will play an integral role in the dissemination process. Members of the PCAG will coauthor academic papers to ensure that the findings are communicated in a manner that is accessible and relevant to families of children with intellectual disabilities.
**2. Academic Publications and Conference Presentations**
The study’s findings will be submitted for publication in peer-reviewed journals that focus on child mental health, intellectual disability, and digital health interventions. Additionally, efforts will be made to present the results at national and international conferences to engage with the broader academic and clinical communities.
**3. Funder’s Website and Public Engagement**
The trial outcomes will be published on the funder’s website to ensure accessibility for the public, including families, health care professionals, and other interested parties.

**4. Collaborations With Specialist Services**
The findings will be shared with the National Health Service specialist mental health services that participated in the trial. These services will receive tailored reports highlighting the practical implications of the study, which may guide the wider adoption of remote video interaction guidance within these settings.

## Abbreviations

CAMHS LD: Child and Adolescent Mental Health Services Learning Disability
CA-SUS: Child and Adolescent Service Use Schedule
DBC-2: Developmental Behaviour Checklist 2 Scale
ESQ: Experience of Service Questionnaire
GDPR: General Data Protection Regulation
ID: intellectual disability
NHS: National Health Service
NICE: National Institute for Health and Care Excellence
PCAG: Parent Carer Advisory Group
PIS: participant information sheet
RCT: randomized controlled trial
SDS: Skills Development Scale
VIG: video interaction guidance
